### **3.1.4 Study design, methodology, study plan**

Persons aged 65 years and older will be recruited in the two selected districts of Nakhon Phanom Province and followed weekly for one year to identify any new episodes of ARI or SARI. Baseline information will be collected from all participants, including functional status and frailty indicators, chronic diseases, smoking history, and variables related to socioeconomic status. Participants will be asked how far the closest health center is from them and household latitude and longitude will be collected in order to calculate distances to medical facilities. ARI will be defined as a new onset of cough or worsening of chronic cough, with or without fever.

SARI will be defined as new onset of cough, worsening of chronic cough or difficulty breathing with a fever  $\geq 38^{\circ}$  Celsius that requires hospitalization. Nasal and nasopharyngeal samples taken from persons with ARI or SARI will be tested using real-time reverse-transcription polymerase chain reaction (rRT-PCR) for influenza and respiratory syncytial viruses. The incidence of laboratory-confirmed, influenza-associated ARI and SARI will be compared between vaccinated and unvaccinated cohort participants, controlling for baseline functional status and underlying medical conditions that might confound the primary association. Data on costs of visits for ARI and SARI for pneumonia or acute respiratory illness will be collected, along with information on the costs of the vaccination campaign, to determine the cost per influenza episode averted and the value for money of the immunization campaign. Results will assist the Thai Ministry of Public Health to make informed decisions related to improving vaccination coverage among the elderly in Thailand.

In addition to vaccine effectiveness and cost effectiveness data, this study will also take the opportunity to measure the effect of ARI and SARI on functional status among the elderly, measure the incidence of influenza-associated COPD exacerbations among those with ARI or SARI, evaluate humoral immune response of IIV3 through measurement of hemagglutination inhibition assay (HAI), and measure the incidence of respiratory syncytial virus (RSV) among the elderly with ARI or SARI.

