## **7.4 Discontinuation Criteria**

Participants in the community study, who choose to withdraw from the study, move permanently outside of the selected sub-district during the study or die during the study period will be considered discontinued. The study will be terminated if any major event results in the inability to contact majority of study participants or to collect adequate data and keep the data safe.

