All participants will be provided a self-swabbing kit from the study team that includes Dacron swabs and test tubes with transport media (TM) which are already labeled with the participants' hospital number, along with written instructions. Participants will be asked to take one nasal self-swab, and to place it in the refrigerator in a separate test tube filled with 1-3ml of TM. Participants will then be asked to describe the procedure to ensure they understand the full technique and will be guided appropriately. Participants will be given a study card with their study ID number and assigned health volunteer's telephone number. Participants who experience an ARI, defined as new onset of cough or worsening of chronic cough, will be asked to take a self-swab as soon as possible and then to call their assigned health volunteer to make an appointment to have their swab collected and answer some questions for the ARI/SARI Episode Questionnaire at the time of the appointment (which will be within 24 hours). The assigned health volunteer will bring an ice box and new Dacron self-swab kit to the sick participant's home, and the specimen will be transported in the ice box by the health volunteer to the sub-district health center for temporary storage. Health volunteers will also conduct the Functional Status Questionnaire three to four weeks after the onset of a participant's ARI or SARI and the Outcomes and Costs of ARI Questionnaire 1 week after the participant recovers which will be monitored through the weekly calls and by the study team. If a participant is very ill due to an ARI and needs assistance in taking a nasal self-swab, they can ask their assigned health volunteer for help in obtaining the specimen. Health volunteers will also be trained to contact their assigned participants weekly to identify ARI events that they have not been notified of already and to take a weekly questionnaire. They will attempt three contacts, by phone or in person, at different times of the day before considering the participant to have missed the week. In the case of an ARI event, participants who have not yet taken a self-swab will be asked to self-swab immediately.

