| 3                                                                                                                                                                                                                           | In the last week, have you been sick with a new, acute illness?        | 1 Yes
2 No
77 Do not know                                                                                        | If no, skip to end of questionnaire |
| In the last week, have you had a NEW:                                                                                                                                                                                       |                                                                        |                                                                                                                        |                                            |
| 4                                                                                                                                                                                                                           | Cough, or a worsening of a chronic cough?                              | 1 Yes
2 No
77 Do not know                                                                                        |                                            |
| 5                                                                                                                                                                                                                           | Fever?                                                                 | 1 Yes
2 No
77 Do not know                                                                                        |                                            |
| 6                                                                                                                                                                                                                           | Nasal discharge/congestion?                                            | 1 Yes
2 No                                                                                                          |                                            |

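### Weekly form 4c ends before the cough question when a participant denies a recent new illness, although the protocol defines ARI by cough alone

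*Protocol*

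**What the plan says.** The case definition in Section 3.1.4 reads: "ARI will be defined as a new onset of cough or worsening of chronic cough, with or without fever". The surveillance paragraph of that section and Section 7.5.1 use the same cough trigger.

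Section 7.5.1 sets up two community routes. A participant with an ARI "will be asked to take a self-swab as soon as possible and then to call their assigned health volunteer to make an appointment". The second route is a backstop: "Health volunteers will also be trained to contact their assigned participants weekly to identify ARI events that they have not been notified of already". The Limitations section relies on it to mitigate forgotten swabs and forgotten calls.

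On the weekly form (Appendix 4c), question 3 asks: "In the last week, have you been sick with a new, acute illness". The instruction for a negative answer is "If no, skip to end of questionnaire". The cough item is question 4, in a block headed "In the last week, have you had a NEW", so it comes after the exit.

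A volunteer makes three attempts "before considering the participant to have missed the week". Neither the form nor Section 7.5.1 gives a longer recall period for the next contact.

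**The concern.** The form applies a narrower filter than the endpoint it feeds. A person can have a qualifying cough without feeling ill, and a chronic cough that has worsened is not obviously a new illness. Someone in that position can answer question 3 negatively in good faith, and the interview ends before the question that defines the case.

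The exit acts on the participants for whom the weekly contact matters most, namely those who did not call and did not attend a facility. Under Section 7.5.1, participants without a working phone are followed by weekly household visits, which are relied on for all their data, and reporting between visits is optional for them. For this group the weekly form is the main community route.

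At stake is ascertainment for objective 1.1, where incidence is a target in its own right alongside vaccine effectiveness (VE). Objective 1.3 may also be touched, because a worsening chronic cough is a natural presentation of a COPD exacerbation.

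**Working it through.** **The three forms side by side**

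| Form | Opening question on recent new illness | What ends the form without a swab |
|---|---|---|
| 4c, weekly contact | Asked; a negative answer ends the form | That answer alone, or later the absence of new or worsening cough |
| 4d, volunteer episode form | Asked; no skip attached | Absence of new or worsening cough |
| 4e, nurse episode form | Asked; no skip attached | Absence of both cough and difficulty breathing |

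Form 4c already carries a cough-based stop after question 7, so the exit at question 3 is a second and narrower filter. Form 4d cannot repair it, because the instruction to complete 4d comes at the end of 4c, after the exit.

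**Look-back.** All symptom items on 4c and 4d cover one week. Onset codes on 4d end at seven days, while 4e has a code for longer ago. An episode that began in a missed week is outside the question at the next contact, and 4d cannot code its onset.

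**Reproducing the planned sample size.** Inputs from Section 7.1.5: 6% yearly incidence, taken as the unvaccinated rate; VE 40%, giving 3.6% in the vaccinated; 1:1 allocation; alpha 5%, taken as two-sided; power 80%. The Fleiss formula is used with p1 − p2 in the denominator.

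- Per group, uncorrected: n = [1.96·√(2 × 0.048 × 0.952) + 0.8416·√(0.06 × 0.94 + 0.036 × 0.964)]² / 0.024² = (0.5925 + 0.2540)² / 0.000576 = 1,244.2.
- With continuity correction: (1,244.2/4) × [1 + √(1 + 4/(1,244.2 × 0.024))]² = 1,326.2, rounded up to 1,327.
- Total 2,654 against the stated 2,724, a difference of 70/2,724 = 2.6%. I treat the plan's figure as reproduced.

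**Equal loss in both groups (assumed 10%, 20%, 30%).** Both rates are multiplied by (1 − loss), so the ratio stays 0.6 and VE stays 40%. Power is for one year at 1,362 per group. Inverting the continuity correction gives n′ = 1,362 − 2/d + 1/(1,362·d²), where d is the rate difference. Then z = [d·√n′ − 1.96·√(2·p̄·q̄)] / √(p1q1 + p2q2).

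| Loss | Rates | n′ | z | Power | N for 80% power |
|---|---|---|---|---|---|
| 0% | 6.00% vs 3.60% | 1,279.9 | 0.88 | 81% | 2,654 |
| 10% | 5.40% vs 3.24% | 1,271.0 | 0.72 | 76% | 2,962 |
| 20% | 4.80% vs 2.88% | 1,259.8 | 0.55 | 71% | 3,348 |
| 30% | 4.20% vs 2.52% | 1,245.6 | 0.37 | 64% | 3,846 |

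**Unequal loss (assumed).** Apparent VE = 1 − 0.6 × (capture in vaccinated)/(capture in unvaccinated). With 90% and 80% captured: 1 − 0.6 × 0.9/0.8 = 32.5%. With 80% and 90%: 1 − 0.6 × 0.8/0.9 = 46.7%.

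**The case against.** The strongest reply is that the weekly form is not the main route. Participants are trained to swab and call when a cough starts, nurses swab those who attend a health centre or hospital, and Section 7.5.1 adds a swab for COPD participants who come to the COPD clinic with an exacerbation. None of these passes through question 3 of form 4c, and an answer of not knowing does not trigger the skip. Loss needs someone who neither reported nor attended and who then denies a new illness despite the cough. This stands: the documents support that ARIs can be lost, not that they are. For COPD, the exposure is confined to episodes that do not reach the clinic.

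The loss fractions are assumptions, and 20% or more of all influenza ARIs may be high for a gate that touches only unreported ones. The power figures are also for one year. If two years are pooled, one-year events of 1,362 × 0.06 + 1,362 × 0.036 = 131 become about 209 after a 20% loss. These split as about 130.8 and 78.4, the standard error of the log rate ratio is √(1/130.8 + 1/78.4) = 0.143, z = 0.511/0.143 = 3.57, and power is about 95%. This stands too, so the power loss is an illustration only.

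A reader might infer that missed weeks are counted as event-free time at risk, because Section 7.4 discontinues only those who "choose to withdraw from the study, move permanently outside of the selected sub-district during the study or die during the study period". The protocol does not say so. Section 7.4 settles who leaves the study, not which weeks enter the denominator. Section 7.9 names person-time at risk as the offset without defining it for missed weeks, form 4c records failed contacts so they can be removed, and a statistical analysis plan may set the rule.

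The Limitations section does admit that some respiratory events will escape. It attributes this to communication, misunderstanding and memory, not to a form that omits the question.

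**Conclusion.** The contradiction is real. Followed as written, form 4c can turn away a participant who meets the protocol's own ARI definition, and it does so in the contact designed to find unreported cases. The one-week look-back with no catch-up, together with the onset codes on 4d, is a smaller gap of the same kind.

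The size cannot be taken from the documents. Under an assumed equal loss of 10% to 30%, incidence is understated by that share, VE is unchanged, and one-year power falls from about 81% to 76% to 64%. A reader might also infer a bias in VE of known sign. The documents do not support one: no form item depends on vaccination, the Limitations section says sicker people are vaccinated more often, and the literature review says lower functional status may go with less vaccination. The unequal-loss figures, 32.5% and 46.7%, lie on either side of 40%. The point should be corrected because the remedy is cheap and bears on the primary endpoint, not because a particular loss has been shown.

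**What to change.** - **Form 4c, question 3:** delete the skip and put the cough item to every participant reached. The cough-based stop already on the form then does the filtering.
- **Look-back:** after a missed contact, ask about the whole period back to the last completed contact, and record the onset date. Make the matching change on form 4d.
- **Form 4d:** add an onset code for more than seven days, as form 4e already has.
- **Late-recalled episodes:** note that they may lack a timely swab. The endpoint is laboratory-confirmed, so the longer look-back will recover fewer confirmed events than it recovers coughs. Removing the skip is the more valuable change.

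The forms are electronic, so the cost is a form edit and a short briefing of volunteers. The downside is a few more swabs for mild cough and some recall error over longer gaps.

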Influenza surveillance: Contact information, including phone numbers, will be recorded for all cohort participants. Health volunteers will contact all participants weekly for one year to identify any individual with new onset of cough or worsening of chronic cough, with or without fever (ARI) and any individuals with cough and fever  $\geq 38^{\circ}\text{C}$  requiring hospitalization (SARI). There are a number of diagnostic specimens that have been used to identify the viral etiology of ARI/SARI, including nasal, nasopharyngeal (NP) and oropharyngeal (OP) swabs. The most acceptable of these to patients is the nasal swab, as it is less invasive (1). Individuals with new onset of cough or worsening of chronic cough will be asked to take a nasal self-swab and properly store the sample in a separate tube. If the participant is too ill to be able to take a self-nasal swab, they will ask their assigned health volunteer to schedule a time to assist them in taking the swab. They will also be encouraged to seek medical attention at the sub-district health center, district hospital or provincial hospital where trained study staff is located if they are feeling very ill. The study will facilitate transport to the local health center for any severely ill participants who are unable to transport themselves. Trained research nurses in the hospital will take nasopharyngeal swabs for influenza diagnosis from admitted participants, and routine clinical information will be recorded. Nasopharyngeal swabs have been shown to be comparable to oropharyngeal swabs for detecting Influenza A and equal or superior to oropharyngeal swabs for detecting Influenza B (2, 3).

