For any participant that does not have a phone or for participants who have a phone without a working signal, we will have the health volunteer follow-up with them on a weekly basis by making household visits instead of a weekly call and rely on this method for collection of all data. If a participant without a working phone develops an ARI or SARI during the week and is able to send someone to the health volunteer to let them know, the health volunteer can also follow-up with the patient using the electronic ARI/SARI Episode Questionnaire, but this is not mandatory for participants without a working phone. If the participant needs to get in touch

with the researcher, the health volunteer will be trained to use their phone to call the researcher for them. When health volunteers transport the specimens to the sub-district health center/district hospital, they will place them inside a refrigerator with a controlled temperature of 2-8°C. Research nurses at the district hospital will be trained to transport the swabs from the refrigerator into the liquid nitrogen tank once a day to keep the specimens below -70°C until transported to NIH.

One research nurse from each health center will be responsible for the enrolled participants within their sub-district. In the event that a participant becomes very ill and goes to the hospital or sub-district health center for treatment of an ARI or SARI, the research nurse at the sub-district health center or district hospital will collect a nasopharyngeal swab from the participant and store it in a refrigerator as outlined in appendix 5a. They will administer the ARI/SARI questionnaire (for health centers) and call the study team to notify them about the participant's visit. The study team will inform the participant's assigned health volunteer so the health volunteer can monitor the participant and take the Functional Status Questionnaire and the Outcomes and Costs of ARI Questionnaire after the participant recovers at the appropriate time period. The nasopharyngeal swabs will also be placed inside a liquid nitrogen tank at the sub-district health centers and district hospitals once a day by trained study team personnel. The nurses at the district hospitals will also collect a nasopharyngeal swab for all participants with COPD who come to the COPD clinic due to an exacerbation.

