| Date                                                                                                                                                                                          | (DD/MM/YY)                                                                                                                                                                            |
| Results                                                                                                                                                                                       | 1 Declined (wishes to discontinue with the study)

Specify reason:

2 Unable to contact (this is the ____ consecutive time)

3 Contact made and interview completed |
| (On phone or in person) Hello, my name is _____ and I am a study team member from the Ministry of Public Health. May I please speak to _____(participant or caregiver of participant)? |                                                                                                                                                                                       |
| [If not a home] When would be a good time to call back to speak to him/her?

_____                                                                                               |                                                                                                                                                                                       |

| No                                                                                                                                                                         | Questions and filters (variable names)                  | Coding categories                       | Skip |
|----------------------------------------------------------------------------------------------------------------------------------------------------------------------------|---------------------------------------------------------|-----------------------------------------|------|
| .                                                                                                                                                                          |                                                         |                                         |      |

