|                                                                                                                                                                                                                                              |                                                          |                                 |  |
|----------------------------------------------------------------------------------------------------------------------------------------------------------------------------------------------------------------------------------------------|----------------------------------------------------------|---------------------------------|--|
|                                                                                                                                                                                                                                              |                                                          | 77 Do not know                  |  |
| 7                                                                                                                                                                                                                                            | Sore throat?                                             | 1 Yes
2 No
77 Do not know |  |
| 
If no report of a new cough or worsening of a chronic cough, please thank patient for their time and let them know that they do not need to take nasal self-swabs this week. Go to end of survey.
                              |                                                          |                                 |  |
| 8                                                                                                                                                                                                                                            | Did you already collect nasal swabs for the new illness? | 1 Yes
2 No
77 Do not know |  |
|                                                                                                                                                                                                                                              |                                                          |                                 |  |

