|                                                                                                                                                                     |                                          |                                                                                                                        |  |
|---------------------------------------------------------------------------------------------------------------------------------------------------------------------|------------------------------------------|------------------------------------------------------------------------------------------------------------------------|--|
|                                                                                                                                                                     |                                          | 77 Do not know                                                                                                         |  |
| If participant answered no for question 2, tell patient they do not need to take nasal swabs at this time and thank them. Go to end of Questionnaire. |                                          |                                                                                                                        |  |
| 6                                                                                                                                                                   | When did this illness begin?             | 1 Today
2 Yesterday
3 2 days ago
4 3 days ago
5 4 days ago
6 5 days ago
7 6 days ago
8 7 days ago |  |
| 7                                                                                                                                                                   | At what time did the illness begin?      | _____                                                                                                                  |  |
| 8                                                                                                                                                                   | What day was the nasal self-swab taken   | MM/DD/YY                                                                                                               |  |

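### The weekly and volunteer episode forms (4c, 4d) do not carry the SARI definition they are meant to serve, so SARI can be classified only where a study nurse sees the patient

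*Protocol*

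**What the plan says.** Section 3.1.4 defines SARI in its opening paragraphs: "SARI will be defined as new onset of cough, worsening of chronic cough or difficulty breathing with a fever" of at least 38 °C that leads to hospitalization. Difficulty breathing is there an alternative to cough. The Influenza surveillance paragraph of the same section sets the task of the weekly contact: "Health volunteers will contact all participants weekly for one year to identify any individual with new onset of cough or worsening of chronic cough", and also "any individuals with cough and fever" of at least 38 °C needing hospitalization. In this version cough is required and difficulty breathing is not mentioned.

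Form 4c (weekly contact) has two stops. If there is no new acute illness, the skip column says "If no, skip to end of questionnaire". If there is no cough, it says "If no report of a new cough or worsening of a chronic cough, please thank patient for their time". Form 4d, although titled for ARI and SARI, has the same kind of stop: "If participant answered no for question 2, tell patient they do not need to take nasal swabs at this time". The result codes of form 4c are declined, completed, and "2 Unable to contact (this is the ____ consecutive time)".

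The nurse route is separate. Section 7.5.1 says that "the research nurse at the sub-district health center or district hospital will collect a nasopharyngeal swab from the participant". Section 7.7 adds that a research nurse looks at the chart of an admitted participant and swabs if applicable. Nurse form 4e asks about difficulty breathing, fever of 38 °C or above, and hospitalization.

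**The concern.** A weekly contact can identify only what its form asks. Two of the SARI criteria (admission and a 38 °C threshold) and the alternative symptom (difficulty breathing) are missing from both volunteer forms. Data never collected cannot be recovered by any later analysis plan, so this is a matter for the protocol and its forms.

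SARI is named beside ARI in primary objective 1.1, and admission costs feed objective 1.2. If SARI is recognised only at facilities with a study nurse, its incidence depends on where the patient went. The Limitations section says that sicker elderly people who see health professionals more often are more likely to be vaccinated. Capture that depends on care-seeking could therefore differ by vaccination group and bias a SARI-specific VE.

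**Working it through.** **Definition against forms**

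| Element | 3.1.4, definition | 3.1.4, Influenza surveillance | Form 4c | Form 4d | Form 4e |
|---|---|---|---|---|---|
| New or worse cough | one of two routes | required | item 4 | item 2 | item 2 |
| Difficulty breathing | the other route | absent | none | none | item 3 |
| Fever of 38 °C or above | required | required | fever yes/no only | fever yes/no only | items 4 and 5 |
| Hospital admission | required | required | none | none | item 8 |
| Ends without swab if | – | – | no new illness, or no cough | no cough | neither cough nor difficulty breathing |

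**Facilities.** The surveillance paragraph of 3.1.4 places trained study staff at sub-district health centers, district hospitals and the provincial hospital. Section 7.5.1 places the swabbing nurse only at the first two. Section 7.7 names no facility. No section gives a route for private or other outside hospitals, although section 7.5.1 (costs) and form 4g expect private care.

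**What happens to an admitted participant**

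1. Study site: form 4e and the chart review can classify SARI, with or without cough.
2. Outside site, with cough, reported and swabbed: counts as ARI. The SARI label is lost.
3. Outside site, with cough, but reported late: forms 4c and 4d ask about new symptoms in the last week, and the onset codes on 4d end at 7 days. A longer illness can be missed altogether.
4. Outside site, difficulty breathing without cough: the volunteer forms stop. The episode is lost, although it is SARI under the first definition.

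**Later forms.** Form 4f asks about any hospitalization, without date, cause or facility. Form 4g asks which facilities were visited. Form 4c schedules both only for participants who were already swabbed.

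**Size.** The documents give no SARI share, so only an illustration is possible. Inputs from section 7.1.5 are 6% yearly ARI incidence, VE 40% (so 6% against 3.6%), 50% vaccinated, and 2,724 participants. The stated size contains no SARI input. The two-proportion formula with continuity correction gives 1,327 per group, 2,654 in all, which is 2.6% below 2,724.

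Expected influenza events in one year: 1,362 × (0.06 + 0.036) ≈ 131.

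Let s be the assumed SARI share of events, and suppose all SARI is lost equally in both groups (power without continuity correction; 0.834 with no loss):

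| s | Events lost | Power |
|---|---|---|
| 2% | 2.6 | 0.827 |
| 5% | 6.5 | 0.814 |
| 10% | 13.1 | 0.792 |

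Now let the missed fraction of SARI be m_v in vaccinated and m_u in unvaccinated participants, with true VE 40%:

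- SARI-only VE = 1 − 0.6 × (1 − m_v)/(1 − m_u). With 10% and 20%: 1 − 0.6 × 0.90/0.80 = 32.5%; reversed, 1 − 0.6 × 0.80/0.90 = 46.7%. With 10% and 30%: 22.9% or 53.3%.
- Combined VE = 1 − 0.6 × (1 − s·m_v)/(1 − s·m_u). With s = 10% and misses of 10% and 30%: 1 − 0.6 × 0.99/0.97 = 38.8%, or 1 − 0.6 × 0.97/0.99 = 41.2%. With s = 2%: 39.8% or 40.2%.

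The combined figures treat every missed SARI as lost outright. They overstate the effect where a case is still swabbed and counted as ARI.

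**The case against.** The protocol assigns SARI to nurses, not to volunteers. Form 4e carries every SARI element and a stop rule covering cough or difficulty breathing, section 7.7 adds chart review on admission, and SARI by definition involves a hospital. At study sites this stands. It does not cover other hospitals, and it does not square with the statement that the weekly contact identifies SARI.

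Forms 4f and 4g, and the record check for costs at public facilities, give later signs of an admission. These are partial: form 4g follows a recorded episode, and neither form records temperature or difficulty breathing.

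Several stronger readings are tempting and are not supported:

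- *That half of the primary endpoint is at risk.* Section 7.9 analyses one combined count of ARI or SARI events, section 7.1.5 sizes on ARI alone, and no SARI share is stated.
- *That the volunteer route misses all SARI.* A SARI with cough also meets the ARI definition. If reported and swabbed, it enters the combined count.
- *That a hospitalised or dead participant can only be coded as not contacted.* The script of form 4c accepts a caregiver, and section 7.4 treats death as discontinuation. What is true is that form 4c has no code for either state.
- *That SARI is the main driver of cost, or that capture favours one vaccination group.* No figure supports the first. The Limitations section does not say which facilities vaccinated people reach.

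Form 4c also shows blank rows after item 8, so the missing items should be confirmed on the electronic form. The cough stop comes before those rows.

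**Conclusion.** The point holds in a limited form. Forms 4c and 4d cannot classify SARI, the two definitions in section 3.1.4 conflict on cough, and the two facility lists differ. SARI classification rests on the study-nurse route alone. Outside admissions have no stated route to it.

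The harm falls mainly on SARI-specific incidence, SARI VE and admission costs. Its size and direction are unknown: the SARI shares and miss rates above are assumptions. If SARI is a small share of events, the combined VE changes little, by about one percentage point in the illustrated range. A SARI-only VE could move by 7 to 17 points under the assumed unequal misses.

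**What to change.** - Reconcile the two SARI definitions in section 3.1.4, and the facility lists in sections 3.1.4 and 7.5.1.
- Add to forms 4c and 4d: difficulty breathing; reported fever of 38 °C or above; and admission to any hospital since the last contact, with hospital and dates. Ask about admission before the new-illness and cough stops.
- Align the stop rule on 4c and 4d with the reconciled definition and form 4e.
- Add result codes to 4c for *currently hospitalised* and *died (date)*, so that outcomes and the person-time offset in section 7.9 are recorded. The enrollment contact form already has a code for death with its date.
- Have the existing research nurses review the chart for any reported admission, classify SARI, and record whether a swab exists. Report SARI without a swab as untested, not as influenza-negative.

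The cost is three items and two codes on electronic forms, some chart reviews, and some extra swabs for difficulty breathing without cough. Two limits remain: temperature reported to a volunteer is self-report, and chart review cannot supply an rRT-PCR result for an admission that was never swabbed.
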